## Abstract

**Background:**

Whiplash injuries are an important public health problem that is associated with significant disability and high health care utilization. Recent cohort studies suggest that physician care may be the most effective treatment for patients with whiplash-associated disorders. However, these findings have not been tested in a randomized controlled trial. The purpose of this study is to determine which of physician care or two rehabilitation programs of care is most effective in improving recovery of patients with recent whiplash associated disorders.

**Methods and Design:**

We designed a pragmatic randomized clinical trial. A total of 444 participants (148 in each of three arms) who reside in Southern Ontario, Canada will be recruited from a large insurer. We will include individuals who are 18 years of age or older and who are diagnosed with Grade I or II Whiplash-associated Disorders. Participants will be randomized to physician-based education and activation or one of two rehabilitation programs of care currently in use in Ontario. Our primary outcome, self-rated global recovery and all secondary outcomes (neck pain intensity, whiplash disability, health-related quality of life, depressive symptomatology and satisfaction with care) will be measured at baseline by a trial coordinator and at 6 weeks, 3, 6, 9 and 12 months follow-up by an interviewer who is blind to the participants' baseline characteristics and treatment allocation. We will also collect information on general health status, other injuries, comorbidities, expectation of recovery, work status, pain coping, legal representation, and co-interventions. The primary intention-to-treat analysis will compare time to recovery between the three interventions. This trial will have 90% power at an alpha of 0.05 to detect a 20% difference in the rate of perceived recovery at one year. Secondary analyses will compare the health outcomes, rate of recurrence and the rate of adverse events between intervention groups.

**Conclusion:**

The results of this study will provide the public, clinicians and policy makers much needed evidence on the effectiveness of common approaches used to manage whiplash-associated disorders.

**Trial registration:**

ClinicalTrials.gov identifier NCT00546806

## Background

Whiplash is the most common traffic injury, affecting 83% of people involved in motor vehicle collisions.[1] The injury leads to "Whiplash-associated Disorders" (WAD), a clinical syndrome that includes neck pain and clusters of physical and psychological symptoms.[2,3] WAD result in a significant burden of pain, disability and health care utilization.[1,2,4-7] Moreover, WAD may increase the risk of future health problems. Studies from Sweden and Saskatchewan suggest that individuals with a history of whiplash injuries may be more likely than those without a history of whiplash injuries to suffer from future episodes of neck pain, headaches, low back pain, shoulder pain, and sleep disturbances.[1,8-10]

Exorbitant health care costs, increasing disability rates and uncertainty about the most effective management of WAD have led governments, insurers and clinicians throughout the Western world to develop treatment guidelines and programs of care for the treatment of whiplash injuries.[1,2,11-15] Traditionally, these guidelines have emphasized the delivery of clinical interventions and focused less on the environment surrounding the claim process. However, it is well known that the recovery from WAD also depends on contextual factors.[1,4,16,17]

A growing body of evidence suggests that the type, intensity and timing of health care delivery are strongly and independently associated with time to recovery. Specifically, Côté et al. found that patients who made more than two visits to general practitioners, more than six visits to chiropractors, received care from general practitioner and chiropractors and those who consulted general practitioners and specialists within the first month of their injury took longer to recover than patients who visited general practitioners once or twice.[4,5] In another cohort, Cassidy et al. investigated the effectiveness of a province-wide rehabilitation program in Saskatchewan and found that patients who attended fitness training or a multidisciplinary outpatient rehabilitation program within 120 days of their injury had slower recovery than those who received usual community care.[11] Finally, a recent randomized trial compared "education and advice" by general practitioners to "education and exercises" by physiotherapists in patients with WAD lasting more than four weeks.[18] One year after the injury, patients in the general practitioner group reported levels of neck pain and headache intensity that were lower than those treated by physiotherapists.[18] Overall, this evidence suggests that the type and intensity of clinical care strongly influences the prognosis of whiplash injuries.

Despite the efforts of governments and insurers, we still do not know whether guidelines or programs of care are effective in improving health outcomes and reducing costs of patients with WAD. To date, no randomized trials have investigated the effectiveness of a coordinated and staged multidisciplinary rehabilitation program aimed at improving the health outcomes of patients with WAD. Moreover, it is not known whether rehabilitation programs are superior to physician-based education and activation in promoting better health outcomes. Therefore, there is a need for a pragmatic randomized controlled trial to investigate which program of care yields the best outcomes for patients.

Our primary objective is to determine whether education and activation by a physician is more effective than two rehabilitation programs of care ("Soft Tissue Injury Care Model" developed by AVIVA Canada and the "Pre-approved Framework Guideline for Grade I and II Whiplash Associated Disorders" developed by the Financial Services Commission of Ontario, an arm's length agency of the Ontario Ministry of Finance) in improving recovery from WAD.

Our secondary objectives will compare the effectiveness of the three interventions on reducing neck pain intensity, reducing whiplash-related disability, improving the health-related quality of life, reducing depressive symptoms, improving satisfaction with care, shorten insurance claim durations, and reducing the recurrence rate in patients with WAD.

## Methods

### Design

We will conduct a three-arm pragmatic randomized controlled trial (Figure 1).

**Figure 1 F1:**
[figure not shown]
**Study Design: Process of recruitment, randomization to treatment, treatment provision, and outcomes assessment**.

### Source population

Eligible for the study are individuals who: 1) are 18 years of age or older; 2) reside or work in the Greater Toronto area, Mississauga, Burlington, Cambridge or Kitchener; 3) are injured in a traffic collision; 4) make an insurance claim for physical injury to AVIVA Canada between February 2008 and March 2011.

### Recruitment

Potential participants will be identified by AVIVA claims adjusters when policy holders contact AVIVA's claim center to report an injury. The adjuster will determine whether the claimant resides or works within the catchment areas of our treatment centers and has sustained a physical injury during the motor vehicle collision. If both these criteria are met, she/he will use a standardized script to invite the claimant to learn more about the trial. Claimants who are interested will be referred immediately to the University Health Network (UHN) trial coordinator who will arrange an appointment at the nearest study clinic to assess the claimant's eligibility for the trial.

### Inclusion and exclusion criteria

All potential participants will be assessed by a trial coordinator to determine whether they meet the inclusion/exclusion criteria (Table 1). The assessment will include a history and physical examination and, if clinically indicated, diagnostic imaging.

**Table 1 T1:** Inclusion and exclusion criteria

**Inclusion criteria**
Diagnosed with Grade I or Grade II WAD
Report an average neck pain since the accident of at least 3 on a 0–10 "Numerical Rating Scale" (NRS)
Able to give written informed consent and complete interviews in English (translators will be available to assist the participant if she/he experiences difficulty understanding specific items on the questionnaire)
Make an insurance claim for physical injury and enroll in trial within 21 days of the traffic collision

**Exclusion criteria**

Fracture/dislocation of the spine or any major bone
Head trauma associated with loss of consciousness
Past whiplash or work-related neck injury within the year prior to their current injury
Active systemic diseases (cancer, inflammatory arthritis, disorders of central nervous system)
Previous neck surgery
Received treatment from a physiotherapist or chiropractor for neck pain in the three months preceding the motor vehicle collision
Individuals who do not reside or work in the Greater Toronto, Mississauga, Burlington, Cambridge or Kitchener areas

### Randomization to treatment groups

Participants will be randomly allocated to one of the three intervention arms after they complete the consent process and answer the baseline questionnaire. If passengers from the same motor vehicle agree to participate, they will be randomized to the same treatment arm to minimize contamination and potentially minimize cross-over between treatment arms. Therefore, our unit of randomization is the motor vehicle. Central randomization was performed by the study biostatistician using statistical package, NQuery Advisor^® ^7.0.[19] To minimize the risk of unbalanced treatment assignment related to patient heterogeneity, we used block randomization which was stratified by clinical centre. The size of the blocks was randomly determined and vary between three, six, nine and 12 participants. The biostatistician provided the trial coordinators with a series of sealed opaque envelopes sequentially numbered by clinical centre. The study biostatistician is not involved in the selection of participants.

### Interventions

Participants randomly assigned to the rehabilitation programs of care will be treated at one of three University Health Network Rehabilitation Solution clinics located at the Toronto Western Hospital in Toronto, and at satellite clinics in Mississauga and Cambridge, which are areas outside of Toronto. All services will be provided by regulated health professionals including physiotherapists, kinesiologists, occupational therapists and massage therapists. Participants allocated to the physician-based "Education and Activation" arm will be referred to family physicians located at Toronto Western Hospital, the Rehabilitation Solutions clinic in Cambridge, and a private clinic in Mississauga. Health care professionals will be assigned to one treatment arm only. As recommended by the Financial Services Commission of Ontario, all participants will receive a "Getting the Facts about Whiplash" brochure. The brochure includes basic information about whiplash.[20]

### Soft Tissue Injury Care Model

The "Soft Tissue Injury Care Model" is a staged multidisciplinary rehabilitation program of care developed by AVIVA Canada. The model aims to reduce the administrative burden related to the claim process and facilitate access to timely health care. Participants randomized to the "Soft Tissue Injury Care Model" will obtain assistance from the clinic staff to complete the insurance forms necessary to initiate the claim. The program will be led by a physiotherapist and includes three integrated and sequential rehabilitation components: 1) Acute-subacute Phase; 2) Multidisciplinary Evaluation and 3) Interdisciplinary Rehabilitation.

#### Acute-subacute phase

During the first six weeks post-injury, care will be delivered by physiotherapists, and if necessary kinesiologists and massage therapists. The care consists of: 1) reassurance; 2) education; 3) home exercises, 4) physiotherapy modalities to reduce pain and 5) massage therapy. A maximum of nine treatments (including massage therapy) during the first three weeks post-collision and an additional eight sessions (including massage therapy) between the third and sixth week post-collision will be allowed. The type and frequency of treatment will be prescribed by the physiotherapist based on her/his assessment. During this phase, the physiotherapist may recommend an "in-home" or "job site" functional assessment. Finally, the physiotherapist will refer the participant to a Multidisciplinary Evaluation if she/he is not progressing as expected.

#### Multidisciplinary evaluation

Patients who require treatment beyond the acute-subacute phase will be referred for a multidisciplinary evaluation. The evaluation will be conducted by an independent team that may include a physiotherapist, physician, occupational therapist, psychologist, and kinesiologist. The purpose of the multidisciplinary evaluation is to identify barriers to recovery and recommend the appropriate treatment through interdisciplinary rehabilitation program.

#### Interdisciplinary rehabilitation

The interdisciplinary rehabilitation program has three specific goals: 1) overcome psychosocial barriers to return to function; 2) physical restoration; and 3) functional restoration. The program will include up to five weeks of daily intervention (each session can last up to 5.5 hours). The frequency, duration and type of care will be determined by the interdisciplinary team. The team may include a physician, physiotherapist, occupational therapist, and a psychologist. Moreover, the following individuals may be invited to join the team: 1) insurance claims advisor; 2) kinesiologist; 3) vocational counselor; 4) employer; 5) ergonomist; and 6) cognitive behavioral therapist. If necessary, the interdisciplinary rehabilitation program will include a jobsite assessment. The services provided during interdisciplinary rehabilitation can include: 1) education; 2) reassurance; 3) goal setting and advice on self-management; 4) psychological counseling and stress management; 5) relaxation therapy, psychotherapy and family counseling; 6) cognitive behavioral therapy; 7) instruction on pain management techniques; and 8) strength, endurance, flexibility or cardiovascular exercises.

### Pre-approved framework guideline for Grade I and II Whiplash Associated Disorders (PAF)

The PAF is a clinical management guideline that focuses on the provision of interventions to manage pain and disability through functional restoration.[20] Its use is mandated in Ontario for patients with Grade I and II WAD.[20] The treatment will be provided under the supervision of a physiotherapist and includes: 1) reassurance; 2) education; 3) home exercises, and 4) encouragement to resume normal activities of daily living. Additionally, the physiotherapist may prescribe the following interventions: 1) exercise and functional activities; 2) mobilization and manipulation; 3) pain management modalities (including massage therapy); and 4) coping skills education. The frequency and number of visits is based on the clinical judgment of the physiotherapist but cannot exceed 10 visits within the first three weeks and nine visits three to six weeks post-collision.

Participants with significant functional limitations will be eligible for a functional assessment of their home, work or school environment. Based on the assessment, occupational therapists will develop an intervention that may include: 1) recommendation to use aids or devices; 2) minor modifications at the work, home, or school environment; 3) instructions on adaptive strategies or alternate approaches to fulfill functional tasks; and 4) specific functional activities to increase tolerance.

Participants who report significant improvement in the first six weeks of care, but who have not recovered, can receive up to four additional treatments over a two-week period. Participants who have not recovered will be re-evaluated and a new plan of management will be developed by the physiotherapist in charge of the care.

### Physician-based education and activation

The education and activation intervention program is designed to promote self-care and early return to normal activities of daily living. Participants randomized to education and activation will be under the care of a family physician.

#### Initial visit

The intervention includes reassurance, education about the favorable prognosis of WAD, encouragement to resume activities of daily living, recommendation to do home exercises (stretching) and, if indicated, prescribe pain relief modalities (heat/ice, acetaminophen or a Cox-2 selective non-steroidal anti-inflammatory drug (NSAID) or non-selective NSAID with or without gastroprotection). At the end of the initial visit, the physician will determine whether a follow-up appointment is necessary or if the participant should be discharged. The participant will be informed to contact the physician should their complaint persist or worsen.

#### Follow-up visits

If follow-up visits are necessary, the participant will be re-assessed and the intervention described above will be repeated and adapted to the participant's status. Participants who have not recovered six weeks after the injury or have improved but require more care will be referred for a multidisciplinary evaluation and enter the interdisciplinary rehabilitation (described above under Soft Tissue Injury Care Model).

### Data collection and follow-up

Table 2 summarizes the data to be collected during the trial. We will follow-up participants at six weeks, and three, six, nine and 12 months post-injury. All follow-up interviews will be conducted by a research assistant either in person at the study clinic or by telephone. The study research assistant will be blind to the treatment allocation and to the baseline characteristics of participants. However, because most outcomes are self-reported by the participants, the research assistant will not be blind to their outcomes status.

**Table 2 T2:** Measures used at baseline and follow-up interviews

**Measures**	**Baseline**	**6 Weeks**	**3 Months**	**6 Months**	**9 Months**	**12 Months**
Accident information	x					

Past history of neck pain and whiplash	x					

Numerical rating scale	x	x	x	x	x	x

Health care after accident	x					

Comorbidity questionnaire	x					

Acute 36-item short-form health survey (V2)	x	x	x	x	x	x

Work status	x	x	x	x	x	x

Expectation of recovery	x	x	x	x	x	x

Whiplash disability questionnaire	x	x	x	x	x	x

Center for epidemiological studies-depression scale (CES-D)	x	x	x	x	x	x

Vanderbilt pain management inventory	x	x		x		

Health state question	x	x	x	x	x	x

Socio-demographic characteristics	x					

Whether a lawyer or paralegal is involved in the claim	x	x	x	x	x	x

Global perceived recovery question	x	x	x	x	x	x

Satisfaction with care and treatment outcome		x	x	x	x	x

Co-interventions		x	x	x	x	x

### Outcomes

#### Primary outcomes

##### Time to recovery

Our primary outcome is time to recovery measured by the global self-perceived recovery question. The global perceived recovery question is a reliable, valid and responsive measure of health status in patients with musculoskeletal disorders.[21] This ordinal transition scale has been used in previous randomized trials and cohort studies of neck pain.[11,22,23] In patients with WAD, we have previously reported that perceived recovery is consistently associated with less neck pain, better physical functioning and fewer depressive symptoms.[11]

At each follow-up interview, participants will be asked: "How well do you feel you are recovering from your injuries?" Participants will select between one of the seven following choices: 1) completely better; 2) much improved; 3) slightly improved; 4) no change; 5) slightly worse; 6) much worse and 7) worse than ever. Participants who respond to be "completely recovered" or "much improved" will be considered recovered. Time to recovery will be measured as the number of days between the date of injury and the first follow-up date at which a participant reports to be "completely recovered" or "much improved".

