### Primary outcomes: self-perceived recovery

Our primary analysis will compare the time to recovery across intervention arms using the Kaplan-Meier method. We will report the median time to recovery and 95% confidence interval (CI).[45] We will use mixed-effect Cox proportional hazards model to measure the effectiveness of the physician-based education and activation intervention and of the Soft Tissue Injury Care Model relative to the PAF. [45-49] Effectiveness will be reported as the Hazard Rate Ratio (HRR) and 95% confidence interval (CI). Participant characteristics that vary between the three interventions at baseline will be included in a multivariable Cox proportional hazards model to control for their confounding effect. Covariates added to the crude Cox Model that change any of intervention regression coefficients by 10% percent or more will be retained as confounders in the adjusted model.[50] The observations of participants who drop out of the study before they report to have recovered will be censored on the date of their last completed follow-up interview. No imputation methods will be used to deal with missing outcomes.

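### Time to recovery is the day of the interview, analysed as an exact event time, so the primary hazard ratio is exposed to any difference between arms in interview timing

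*Protocol article*

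**What the plan says.** Protocol article, Time to recovery: the event time is "the number of days between the date of injury and the first follow-up date at which a participant reports" one of the top two of seven answers. The event rule reads "Participants who respond to be 'completely recovered' or 'much improved' will be considered recovered".

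Data collection and follow-up: "We will follow-up participants at six weeks, and three, six, nine and 12 months post-injury". Interviews are "conducted by a research assistant either in person at the study clinic or by telephone", and "The study research assistant will be blind to the treatment allocation and to the baseline characteristics of participants". Table 2 also marks the recovery question at baseline.

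Statistical analysis of the primary outcome: "Our primary analysis will compare the time to recovery across intervention arms using the Kaplan-Meier method". The median with a 95% confidence interval is reported, and a mixed-effect Cox model gives the hazard rate ratio. Participants who drop out unrecovered are right-censored at their last completed interview, and missing outcomes are not imputed.

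Inclusion criteria: enrolment is possible up to 21 days after the collision, and the pain criterion is "Report an average neck pain since the accident of at least 3" on a 0-10 scale, which is not current status. Neither the inclusion nor the exclusion criteria refer to recovery status at entry.

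**The concern.** A participant who is recovered at one interview and was not at the previous one recovered at some point between the two. The recorded day is the day the question was asked. Kaplan-Meier and Cox take that day as the event time, with two consequences.

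- The curve can step only on interview days, so the median is an interview date. It falls at or after true recovery, with a confidence interval that ignores the width of the gap.
- The Cox model uses only the order of event times. Within a wave, that order is the order of the interviews. If one arm is systematically reached later, its events rank later even when equally many have recovered.

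A separate, smaller matter is the baseline answer. A person already much improved when enrolled satisfies the eligibility criteria, is counted only from follow-up, and so typically becomes an event at six weeks in any arm. Such participants carry no information on treatment and pull the hazard ratio towards 1.

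At stake are the primary hazard ratio and the headline median.

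**Working it through.** **The plan's own figures.** The protocol gives no figure on this point. Its 114 per group cannot be confirmed, because no control recovery rate is stated; it is reachable under assumed rates (for example, Schoenfeld's formula gives 114 at 51% against 71%). For scale, 148 enrolled per arm with the stated 30% loss leaves 148 × 0.70 = 103.6, about 104.

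**How late the recorded day can be.** With the waves at about days 42, 91, 182, 273 and 365, the gaps between them are 49, 91, 91 and 92 days. A recovery can therefore be recorded up to seven weeks late at the second wave and about thirteen weeks late at later ones, and later still after a missed interview.

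**Why order matters.** Take one wave with n at risk and d recovered in each of two arms.

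- All interviewed on the same day: expected events in arm A are 2d × n/(2n) = d, so observed minus expected is 0.
- Arm A interviewed first, arm B a few days later: expected events in A are d/2 + d(n − d)/(2n − d). Observed minus expected is d − d/2 − d(n − d)/(2n − d) = d²/[2(2n − d)], which is above 0.

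Arm A appears to recover faster although the same number recovered. If timing is the same in both arms, the effect vanishes.

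**Simulation, no true effect.** Every input here is an assumption: exponential recovery, the delay of one arm, and random scatter of interview dates. Setting S uses symmetric normal scatter (SD 7 days), 104 per arm, 60-80% recovered at one year and 500-600 trials where the count is recorded. Setting O uses one-sided scatter (never early, absolute value of the same normal), 148 per arm, 50% or 70% recovered and 1,000 trials.

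| Mean delay in one arm | S, by interview day | S, by wave | O, by interview day | O, by wave |
|---|---|---|---|---|
| 0 days | HR 1.00, 5-7% false positives | not reported | 1.00, 4-5% | 1.00-1.01, 5% |
| 3 days | 0.94, 5-8% | not reported | 0.90, 12% | 1.01-1.02, 4-5% |
| 7 days | 0.85-0.88, 12-16% | 1.03-1.04, 4-7% | 0.80-0.82, 26-30% | 1.02, 5-7% |
| 14 days | not reported | not reported | 0.76-0.78, 37-41% | 1.05-1.06, 5-6% |

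O is worse mainly because its scatter is narrower: the SD of the absolute value is 7 × √(1 − 2/π) = 4.2 days, so a given delay reorders more events. With O's scatter and 104 per arm, 7 days gives 0.81-0.82 and 23-24%. Monte Carlo error for a rate of 14% in 600 trials is √(0.14 × 0.86/600) = 1.4 points. The by-wave hazard ratio lies slightly above 1 because the later arm has a few more days in which to recover before each interview.

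**True hazard ratio 1.5, setting O.** With a common schedule the interview-day Cox model returns 1.48-1.50. With a 7-day delay in the faster-recovering arm it returns 1.20-1.23, against about 1.54 by wave. Missed interviews alone (20% against 30% by arm) matter little: 0.98-1.00 under the null and 1.44-1.47 for a true 1.5.

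**Already improved at baseline.** The share is not in the protocol. If it were 5%, 10% or 20%, a hazard ratio of 1.5 among the others would be estimated as 1.43-1.46, 1.40-1.41 or 1.34-1.35, with type I error still near 5%. The loss of power depends on whom the planned difference describes. Taking 54% against 74% (a pair at which Freedman's formula gives 115 per arm), a share of 10% or 20% lowers power of about 90% to 84% or 73% if those rates apply only to participants not yet recovered, and to about 87% or 84% if they apply to everyone enrolled.

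**The case against.** The strongest reply is that nothing in the protocol shows interview timing to differ by arm. One schedule, counted from injury, applies to all; the interviewer is blind to allocation; telephone interviews are open to everyone. The physician arm shares Toronto Western Hospital and the Cambridge clinic with the rehabilitation arms. A shift of 7 days at every wave is invented, and at 3 days with symmetric scatter the error rate is close to nominal. The full protocol may also set an interview window, which would bound any delay. The endpoint is openly defined as first reported recovery at follow-up, so some of the lateness is definition.

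Most of this stands. A reader might infer that the planned hazard ratio is biased; the documents do not support that. What remains is exposure. The rehabilitation arms allow up to 17 (9 + 8) or 19 (10 + 9) sessions in six weeks, a physician-arm participant may be discharged after one visit, and four of 12 pilot participants could not be reached at six weeks. Blinding the interviewer does not equalise how easily participants are reached.

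Two further stronger readings fail. Participants improved at baseline do not create false positives when arms are balanced; they dilute. Nor is the single hazard ratio invalid because in the physician arm "Participants who have not recovered six weeks after the injury or have improved but require more care will be referred for a multidisciplinary evaluation": that step belongs to the assigned strategy, and the protocol declares a treatment-policy analysis.

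**Conclusion.** The point holds as a weakness of a stated method, not as a demonstrated bias. Recovery known only to lie between interviews is analysed as if its day were known. The median is therefore late and over-precise whatever the schedule. The hazard ratio is unbiased under common timing. Under an assumed 3- or 7-day average delay in one arm with symmetric scatter, a null value becomes about 0.94 or 0.87 with about 5-8% or 12-16% false positives; narrower scatter makes this worse. Analysis by wave keeps it at about 1.03 with near-nominal error. Delay, scatter and recovery rates are all assumptions. The dilution from participants already improved at entry is real in direction, but the protocol does not allow its size to be computed. The change is worth making because it is cheap and removes almost all of the exposure.

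**What to change.** - Make the primary effect model a discrete-time complementary log-log model by scheduled wave (its coefficient is still a log hazard ratio), or an interval-censored model. Include all randomised participants, let a missed interview widen the interval, and keep a random effect for the vehicle, the unit of randomisation.
- Report the median as an interval between waves, and keep the day-based Kaplan-Meier and Cox analyses as sensitivity.
- Add the baseline answer to the recovery question as a pre-specified covariate. The planned rule, which considers characteristics that differ between arms, would not bring it in when arms are balanced, yet dilution occurs then too.
- Exclude participants already in the top two categories at baseline in a sensitivity analysis only. Excluding them from the primary analysis would depart from the declared intention-to-treat analysis and reduce the sample.

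The cost is analysis wording, to be settled before outcomes by arm are seen. No new data are needed. The median becomes coarser, and a by-wave model still leaves a small residual (about 1.03 at a 7-day delay), which an interval-censored model using actual interview dates should reduce.
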